### Intervention description {11a}

After confirming eligibility based on the inclusion/exclusion criteria, the target knee (left or right) for evaluation will be selected. If only one knee meets the criteria for PFP, that knee will be selected. If both knees qualify, the knee with greater pain will be chosen. All subsequent evaluations will be conducted on the knee selected as the target knee for assessment.

The investigational medical device “MORA Cure PFP” used in this study will be applied only to participants assigned to the treatment group. MORA Cure PFP consists of a web platform for healthcare professionals and a mobile application for patients. The investigator prescribes treatment through the healthcare web platform, and participants install the application on their mobile phones to begin therapy. At baseline, the investigator will randomize and enroll participants. For those assigned to the treatment group, the investigator will register them on the healthcare web platform and prescribe the device. Upon prescription, an installation code for the patient app will appear on the web platform. Participants will then follow the installation manual to install the app, agree to the terms of service, complete registration, and start the plan, with the Day 1 program beginning on the same day. The device provides an 8-week program of rehabilitative exercise and cognitive behavioral therapy (CBT) for PFP (Fig. 2). After the initial 8-week treatment period, participants can retain access to the device for up to 12 weeks.

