### Participant timeline {13}

Participants in this clinical trial will complete 4 to 5 outpatient visits: V1 (Screening), V2 (Baseline), V3 (In-treatment), V4 (Post-treatment), and V5 (Follow-up). V2 must occur within 4 weeks of V1 and may be conducted on the same day as V1. V3 is scheduled 4 weeks after V2, with an allowable range of 3 to 5 weeks. V4 is set for 8 weeks after V2, with a window of 8 to 9 weeks, and V5 is scheduled 12 weeks after V2, with an allowable range of 12 to 13 weeks. See Table 2 for the specific schedule of assessments for each visit. For Visit 3, participants may not need to visit the medical institution in person. In this case, certain checks, such as prior medication, concomitant medication, and adverse event assessments, may be omitted. Pain intensity assessment and the Kujala evaluation will be conducted by sending a survey link to the participant, who will complete it while in contact with the clinical trial site representative over the phone.

**Table 2 Tab2:** Assessment schedule by visit

Schedule	Screening (V1)	Baseline (V2)^1^	In-treatment (V3)^2,3^	Post-treatment (V4)^4^	Follow-up (V5)^5^
	− 4 weeks ~ 0 week	0 week	3 weeks ~ 5 weeks	8 weeks ~ 9 weeks	12 weeks ~ 13 weeks
Informed consent	X				
Screening number assignment	X				
Demographics	X				
Medical history	X				
Height and weight measurement		X			
Physical examination	X	X	X^3^	X	X
Concomitant/previous medication history	X	X	X^3^	X	X
Knee X-ray Imaging and K-L grading	X^6^				
Inclusion/exclusion criteria review	X	X			
Selection of target knee (L/R)		X			
Randomization and assignment of registration number		X			
Pain intensity assessment		X	X	X	X
Kujala questionnaire		X	X	X	X
EQ-5D-5L questionnaire		X		X	X
PHQ-9 questionnaire		X		X	X
PCS questionnaire		X		X	X
Overall perceived recovery score assessment				X	X
Disease education		X			
Investigational device prescription and app installation (treatment group only)		X			
Education on self-exercise (control group only)		X			
Self-exercise patient diary distribution (control group only)		X			
Self-exercise patient diary return (control group only)			X^7^	X^7^	X
Adverse event review		X	X^3^	X	X
Investigational device app deletion (treatment gropu only)					X

1. V2 must be conducted within 4 weeks of V1, and V1 and V2 can take place on the same day

2. V3 is conducted 4 weeks after V2, with a permissible variation of one week before or after (3 to 5 weeks)

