### Outcomes {12}

The primary efficacy outcome of this trial is usual pain intensity score (VAS, 100 scale) at 8 weeks (V4). For secondary outcomes, see Table 1. For the method of aggregation, all outcome measures will be analyzed as continuous variables using mean values with appropriate statistical comparisons between groups (For further detail, see Statistical Analysis).

Through interviews, demographic information, medical history, surgical history, and prior/concomitant medications will be collected. Physical examination will include measurements of height, weight, and a patella examination. A knee X-ray will be taken to assign a K-L grade [40], which is used to assess exclusion criteria for osteoarthritis.

The usual and worst pain intensity scores assess the average and peak knee pain experienced over the past week, respectively. Participants mark their pain level on a visual analog scale from 0 to 100, with values recorded and rounded to the nearest whole number [41].

To assess knee function, participants complete the anterior knee pain scale (Kujala score), 13-item self-report questionnaire [42], with a total score calculated from the responses. Quality of life is assessed via the EQ-5D-5L [43] questionnaire, recording the sum of scores across five questions and today’s health status score. Depression severity is evaluated using the Patient Health Questionnaire-9 (PHQ-9) [44], with a total score from nine questions, while pain catastrophizing is assessed using the Pain Catastrophizing Scale (PCS) [45], totaling scores from 13 questions. Participants also rate their perceived recovery level on a 0 to 6 scale [46].

All pain and questionnaire assessments are conducted as electronic patient-reported outcomes (ePRO). Participants use digital tools provided at the site, with data automatically transferred to the electronic case report form (eCRF). For visit 3, if conducted as a televisit, participants may complete the assessments remotely.

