### Provision for post-trial care {30d}

After completing or withdrawing from the clinical trial, participants may resume regular medical care as before. If an adverse device effect arises, they may be compensated for medical expenses per the compensation policy until the issue is resolved. The sponsor will secure IRB approval for the insurance policy covering such compensation. Additionally, if there is any suspicion of an adverse event after a participant’s trial completion or withdrawal, the investigator must assess and provide further medical care as needed.

Participants will not be able to continue accessing the app after the trial period ends. The investigational medical device will be deleted from participants’ mobile phones at V5 (end of trial period), as access to unapproved medical devices by study participants must be limited to the minimum necessary for the trial.

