## Statistical methods

### Definition of analysis sets

In this clinical trial, data will be analyzed using three sets: the full analysis set (FAS), the per protocol set (PPS), and the safety set. The FAS, aligned with the intention-to-treat (ITT) principle, will be the primary analysis set for efficacy evaluations, with additional analyses using the PPS. If discrepancies arise between the two, the outcomes will be presented and investigated. Safety evaluations will use the safety set.

The FAS includes participants who meet all of the following: have post-randomization primary efficacy data, records of applying the investigational device (test group) or performing self-exercise (control group), and were not improperly enrolled due to inclusion/exclusion violations. The PPS is a subset of the FAS, including those who completed the trial without major protocol violations, did not withdraw prematurely, and had an overall compliance rate of 50% or higher. The safety set includes all randomized participants with records of using the investigational device or performing self-exercise.

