In designing clinical trials for digital therapeutics, specific considerations are essential. For instance, some trials use a “sham device,” a simplified app lacking therapeutic features, as the control group [51]. However, this trial aims to demonstrate the app’s superiority over the at-best treatment (treatment-as-usual). Therefore, the control group will receive in-person exercise education with materials and resources for self-guided exercise without app use. The inclusion/exclusion criteria should accurately represent the indication. In this trial, PFP guidelines [11–14] are used to select participants with chronic patella-related pain lasting over 3 months and confirm objective pain elicited through movement or physical exams. Given that PFP is often diagnosed by exclusion [11–14], patients with conditions such as osteoarthritis, fractures, dislocations, surgical history, or patellar tendinitis are excluded. Additionally, patients requiring high-potency drugs like narcotic analgesics are beyond the app’s intended use and are excluded. The required participant number is designed based on the app’s feasibility trial [35], offering a more objective basis than calculations based on non-app studies. As the name implies, PFP is characterized primarily by pain, so the primary endpoint is the usual pain level at 8 weeks, with expectations that the app group will report lower pain levels than the control group.

A representative digital therapeutic for knee-related conditions is Mawendo (manufactured by Mawendo GmbH, Germany). In Germany, digital therapeutics are covered under the category of Digitale Gesundheitsanwendungen (DiGA) by public health insurance (Gesetzliche Krankenversicherung, GKV), and Mawendo accounts for approximately one quarter of the total reimbursement within the DiGA category [52]. A randomized controlled trial involving 259 participants showed statistically significant therapeutic superiority of Mawendo over standard physiotherapy [53]. Its primary outcomes are functional improvement, as measured by knee injury and osteoarthritis outcome score-activities of daily living subscale (KOOS-ADL), and pain reduction, assessed using VAS. While Mawendo’s typical treatment period spans 12 weeks, this study will include an 8-week treatment phase followed by a 4-week extra curriculum. An additional difference of this study is its inclusion of psychological measures, evaluating depression and pain catastrophizing levels.

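### The single per-protocol set requires completing the trial to V5, so withdrawals or major violations after V4 remove observed week-8 primary scores from the supportive analysis

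*Protocol article*

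**What the plan says.** The section Definition of analysis sets makes the FAS the primary set for efficacy and the PPS an additional one. Membership of the PPS is drawn from the FAS and restricted as follows: "including those who completed the trial without major protocol violations, did not withdraw prematurely, and had an overall compliance rate of 50% or higher". No endpoint-specific version is given. The section adds that differences between FAS and PPS results will be reported and looked into.

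The timing comes from other sections:

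- Outcomes {12} places the primary outcome, usual pain on a 0 to 100 VAS, at 8 weeks (V4).
- Intervention description {11a}: "The device provides an 8-week program of rehabilitative exercise and cognitive behavioral therapy (CBT) for PFP". It continues: "After the initial 8-week treatment period, participants can retain access to the device for up to 12 weeks".
- Participant timeline {13}: "V5 is scheduled 12 weeks after V2, with an allowable range of 12 to 13 weeks".
- Provision for post-trial care {30d} identifies V5 as the end of the trial: "The investigational medical device will be deleted from participants’ mobile phones at V5 (end of trial period".
- The section on concomitant care {11d} runs its prohibitions from visit 1 to visit 5. The section on discontinuation {11b} lists grounds for withdrawal, including unapproved treatment and loss to follow-up, and does not limit them to the first 8 weeks.

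**The concern.** A per-protocol analysis of a week-8 outcome should ask what the comparison looks like among people who followed the plan up to week 8. This definition asks for about four more weeks of good conduct. Those weeks cannot have influenced the V4 score, but the V4 score may influence them: people who have recovered may stop attending, and people who are disappointed may leave or seek a prohibited treatment. The trial is open-label, so such behaviour could also differ by arm, although nothing in the document shows that it will.

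At stake is the value of the PPS as a check on the FAS. If the two results differ, the difference is meant to say something about adherence to treatment. Under the present definition part of it may instead come from selection on events after the outcome, and part of any agreement may be accidental.

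**Working it through.** **Step 1: who is excluded.** Take a participant with a complete 8-week course, good compliance and a recorded V4 score, who withdraws consent at week 10.

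- FAS: post-V4 withdrawal is not among its exclusion criteria, and {11b} keeps withdrawn participants in the efficacy evaluation unless there is a valid reason to exclude them. The V4 score counts.
- PPS: the participant has not completed a trial that ends at V5 and has withdrawn early. The V4 score does not count.

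The same follows for loss to follow-up after V4, and for a major violation after V4, since the prohibitions run to V5.

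**Step 2: the plan's own sample size.** Inputs from Sample size {14}: effect size 0.428, two-sided 0.05, power 0.80, dropout 20%.

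- n per group = 2 × (1.960 + 0.842)² / 0.428² = 85.72, rounded up to 86.
- Inflated: 86 / (1 − 0.20) = 107.5, rounded up to 108 per group, 216 in total.

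The stated figures reproduce, and this point does not change them.

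**Step 3: how many could be affected.** The plan gives no timing for the 20%. Read it as dropout over the whole trial, and let f be the share that falls after V4 (an assumption, shown over its full range).

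- Completing V5: 216 × 0.80 = 172.8
- Reaching V4: 216 × [1 − 0.20 × (1 − f)]
- Excluded for post-V4 dropout: the difference, 43.2 × f

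| f | Reach V4 | Complete V5 | Excluded for post-V4 dropout |
|---|---|---|---|
| 0 | 172.8 | 172.8 | 0 |
| 0.25 | 183.6 | 172.8 | 10.8 |
| 0.50 | 194.4 | 172.8 | 21.6 |
| 0.75 | 205.2 | 172.8 | 32.4 |
| 1 | 216.0 | 172.8 | 43.2 |

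For scale, the printed pilot means and SDs give |d| = 0.87 / 2.016 = 0.432. With power = Φ(|d|√(n/2) − 1.96) and n per group, 172.8 participants give 0.81. Keeping everyone with a V4 score gives 0.81 (f = 0) to 0.89 (f = 1). These are nominal values for a supportive analysis, before any exclusion for compliance or violations. Selection matters more here than the loss of power.

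**The case against.** The strongest reply is that the PPS is only supportive. The confirmatory test, its type I error and the sample size all rest on the FAS, which keeps the V4 score of a late leaver. This stands, and it limits the weight of the point.

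A second reply is that one completer set serves both the week-8 and the many week-12 secondary endpoints, and that every PPS conditions on behaviour after randomisation. The first half justifies V5 completion for week-12 endpoints but not for week 8. The second half is true. Still, conditioning on conduct before the outcome is the purpose of a PPS, and conditioning on conduct after it has no such purpose.

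A third reply is that the full protocol or SAP may refine the definition. That would excuse an omission, but the completion criterion is stated in the article and fits the primary endpoint badly.

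Two stronger readings are not supported:

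- **Compliance.** A reader might infer that the 50% rule also penalises those who stop at week 8, because it refers to *overall* compliance. Over 12 weeks with no activity after week 8, compliance c in weeks 0 to 8 must satisfy c × 8/12 ≥ 0.50, that is, c ≥ 75%. But the article gives no window for the rate, which may cover only the 8-week programme, and a condensed article may leave that formula to the full document. Nor is it clear that stopping at week 8 is free. The adherence section {11c} requires daily self-treatment without an end at week 8, control diaries are returned up to V5, and the Discussion says "this study will include an 8-week treatment phase followed by a 4-week extra curriculum". Neither the 75% threshold nor an exclusion under this rule for conduct in weeks 9 to 12 should be asserted.
- **A missed V5 visit.** This alone is not clearly an exclusion. Section {11b} treats a missed visit separately from withdrawal and loss to follow-up, and the PPS is analysed without imputation, so some missing values are foreseen.

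**Conclusion.** The point holds for completion, withdrawal and major violations: as written, events between V4 and V5 can remove an observed week-8 primary score from the PPS.

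The size is unknown. On the plan's 20% dropout, read as whole-trial dropout, the range is 0 to about 43 of 216. The lower end is as compatible with the text as the upper. Post-V4 major violations without withdrawal would add to the count; people already outside the PPS for earlier reasons would reduce it. If the 20% was meant as loss before V4 only, the plan says nothing about how many leave later.

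Neither a bias in a given direction nor a difference between arms is shown. The consequence is confined to the supportive PPS result and to the FAS/PPS comparison. It is worth correcting because the correction is small and keeps that comparison interpretable.

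**What to change.** Before database lock, define PPS membership by endpoint:

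- **Week-8 endpoints:** in the FAS, with an observed V4 outcome, no withdrawal and no major violation up to V4, and at least 50% compliance computed over weeks 0 to 8 in both arms. Events after V4 do not affect membership.
- **Week-12 endpoints:** keep the requirement of completing the trial to V5.

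Stating the weeks 0 to 8 window also settles which period the compliance rate covers for the primary endpoint.

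The cost is a few sentences in the analysis-set definition and two versions of the PPS to program, label and report. The plan must also say which version serves the week-4 secondary endpoints. No new data are needed, and the FAS analysis and sample size stay as they are.

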### Methods in analysis to handle protocol non-adherence and any statistical methods to handle missing data {20c}

For the analysis of the FAS, missing values occurring after treatment that are used for primary and secondary efficacy evaluation variables will be imputed using the last observation carried forward (LOCF) method. However, when imputing missing values, results prior to the administration of the investigational medical device will not be substituted for post-administration results. Other data will be analyzed as collected (available data) without imputation.

For the analysis of the PPS, missing values will not be imputed and will be analyzed as collected.

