### Sample size {14}

The primary efficacy variable of this clinical trial is the intensity of usual pain over the past week at 8 weeks post-treatment initiation, aiming to assess whether the experimental group shows superior improvement compared to the control group. The hypothesis for the superiority test on the primary efficacy variable is as follows: $${H}_{0}: {\mu }_{t}={\mu }_{c} vs. {H}_{1}: {\mu }_{t}\ne {\mu }_{c}$$, where $${\mu }_{t}$$ represents the usual pain intensity at 8 weeks for the experimental group, and $${\upmu }_{\text{c}}$$ represents the same for the control group.

The sample size was calculated based on prior study of MORA Cure PFP (ClinicalTrials.gov., NCT05614583). In the exploratory clinical trial, the usual pain over the past week of full analysis set at 8 weeks post-treatment was 2.31 ± 1.49 for the experimental group and 3.18 ± 2.43 for the control group [35]. The calculated effect size (Cohen’s *d*) is as follows: $$d=\frac{{m}_{t}-{m}_{c}}{\sqrt{\left({s}_{t}^{2}+{s}_{c}^{2}\right)/2}}=\frac{2.31-3.18}{\sqrt{\left({1.49}^{2}+{2.43}^{2}\right)/2}}=-0.428$$, where $${m}_{t}$$ is mean of the experimental group, $${m}_{c}$$ is mean of the control group, $${s}_{t}$$ is standard deviation of the experimental group, and $${s}_{c}$$ is standard deviation of the control group [47]. Values were used up to the second decimal place, and the effect size was calculated without rounding.

Using an effect size of − 0.428, a Type I error of 0.05, and a power of 0.8, the formula for calculating the sample size per group is: $$n=\frac{2{\left({z}_{1-\alpha /2}+{z}_{1-\beta }\right)}^{2}}{{\left(d\right)}^{2}}=\frac{2{\left(1.960+0.842\right)}^{2}}{{\left(0.428\right)}^{2}}=86$$, where $$n$$ is required sample size per group (rounded up to the nearest whole number), $$\alpha$$ is Type I error, $$\upbeta$$ is Type II error (1 − power), and $$d$$ is effect size [47].

Considering a typical dropout rate of 10–30% for clinical trials involving digital services [48], a 20% dropout rate was assumed for this study. Adjusting for this dropout rate, the required sample size per group is calculated as: $${n}^{\text{'}}=86\times \frac{1}{1-r}=107.5$$, where *r* is the dropout rate (0.2). Thus, the target sample size is set at 216 participants in total, with 108 per group (Fig. 1).

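### Single-value LOCF as the primary missing-data method puts a week-4 pain score in place of week 8 for up to the assumed 20% dropout, which can bias the primary comparison in either direction

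*Protocol article*

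**What the plan says.** The missing-data section {20c} states that, in the FAS, post-treatment values missing for "primary and secondary efficacy evaluation variables will be imputed using the last observation carried forward (LOCF) method". It adds one limit: "results prior to the administration of the investigational medical device will not be substituted for post-administration results".

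Under Definition of analysis sets, the FAS "will be the primary analysis set for efficacy evaluations, with additional analyses using the PPS". To enter it a participant must, among other conditions, "have post-randomization primary efficacy data".

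The PPS follows a different rule: "For the analysis of the PPS, missing values will not be imputed and will be analyzed as collected". It is restricted to FAS members who completed without major violations, "did not withdraw prematurely, and had an overall compliance rate of 50% or higher".

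The primary endpoint is usual pain on a 0 to 100 VAS at week 8 (V4), compared by ANCOVA with baseline as covariate. Table 2 schedules pain at V2, V3, V4 and V5. On timing, the Participant timeline says "V3 is scheduled 4 weeks after V2, with an allowable range of 3 to 5 weeks". Under Sample size, "a 20% dropout rate was assumed for this study", with no split by arm or by time of dropout.

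**The concern.** V3 falls about halfway through an 8-week programme. Carrying it to week 8 assumes that pain stays flat over the second half of treatment in everyone who leaves. The method gives the filled value the same weight as a measured one, and it ignores the week-12 score of a participant who misses only V4.

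The article describes conditions under which dropout could differ between arms or depend on pain. The trial is open-label. Automated reminders and personalised messages are described only for the app. Receiving unapproved treatment leads to withdrawal. If the arms differ in who is imputed or in how pain moves after week 4, LOCF passes that difference into the treatment effect. At stake is the primary comparison of a confirmatory superiority trial meant to support device approval.

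**Working it through.** **The plan's own figure.** With d = 0.428, n = 2(1.960 + 0.842)²/0.428² = 85.72, rounded up to 86 per group. Then 86/0.8 = 107.5, set to 108 per group and 216 in total. This reproduces the article. The 20% is treated there as contributing nothing.

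**Who is imputed.** Baseline cannot be carried forward and the FAS needs post-randomization data, so for the primary endpoint only participants with V3 but no V4 are imputed. Let s be the share of the 20% who leave after giving a V3 score. The number imputed per arm is 108 × 0.20 × s, and the fraction of the FAS is 0.20s/(0.80 + 0.20s).

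| s | imputed per arm | fraction of FAS |
|---|---|---|
| 0 | 0 | 0% |
| 0.25 | 5.4 | 5.9% |
| 0.50 | 10.8 | 11.1% |
| 0.75 | 16.2 | 15.8% |
| 1 | 21.6 | 20% |

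**Bias formula.** Let q be the imputed share of an arm and g the mean of (week-4 pain minus true week-8 pain) among those imputed. The LOCF bias in app minus control is q_t·g_t − q_c·g_c. A negative value favours the app.

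**Inputs.** The pooled pilot SD is √((1.49² + 2.43²)/2) = 2.016 and the pilot difference is 2.31 − 3.18 = −0.87. I assume the pilot scores are on a 0–10 scale, so on the 100-point endpoint these become 20.2 and 8.7. Assumptions not found in the article: pain correlations of 0.5 (baseline–week 4), 0.4 (baseline–week 8) and 0.65 (week 4–week 8), the dropout split, all dropout after V3, and the mean fall from week 4 to week 8. The standard error is about 20.2 × √(1 − 0.4²) × √(2/108) = 2.5. With z = bias/2.5, two-sided rejection is 1 − Φ(1.96 − z) + Φ(−1.96 − z).

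**No true week-8 effect, 108 per arm.**

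| Dropout, app vs control | Fall, week 4 to 8 | Bias by formula | Type I error |
|---|---|---|---|
| 20% vs 20% | 10 in both | 0.20×10 − 0.20×10 = 0 | 5% |
| 10% vs 30% | 0 | 0 | 5% |
| 15% vs 25% | 5 | 0.15×5 − 0.25×5 = −0.5 | about 5.5% |
| 10% vs 30% | 5 | 0.10×5 − 0.30×5 = −1.0 | about 7% |
| 15% vs 25% | 10 | 0.15×10 − 0.25×10 = −1.0 | about 7% |
| 10% vs 30% | 10 | 0.10×10 − 0.30×10 = −2.0 | about 12% |

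Simulation agrees with these rows; the two cases of −1.0 came out at up to 1.1 points. If, in the last row, control dropout also rises with week-4 pain, simulation gives about 3 points and 20%. The exact figure depends on how strong that link is. Swapping the arms reverses the sign.

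**True effect of 8.7 at week 8 and 4 at week 4, with 20% dropout in each arm.** LOCF estimates 0.80 × 8.7 + 0.20 × 4 = 7.76, about 7.8. That is 0.94/8.7 = 11% too small.

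**Comparison.** A likelihood fit that uses the week-4 score recovers the true value to within 0.1 point in these scenarios. This is by construction, because dropout was either random or dependent on week-4 pain, which that model contains.

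**The case against.** Several stronger readings are tempting, and the article does not support them.

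- **That the whole 20% is imputed.** It is not: anyone lost before V3 is excluded. The 20% is a ceiling, and half of it leaving before V3 would put about 11% of the FAS under imputation.
- **That bias follows whenever dropout or time course differs.** It does not. Flat pain after week 4 gives none, and differences can cancel: 10% vs 30% imputed with falls in the ratio 1.0 to 0.33 gives 0.10 × 1.0 − 0.30 × 0.33, which is essentially 0.
- **That baseline may be carried forward in controls only, because the rule refers to the device.** This is a strained literal reading. The article also defines treatment-emergent events by application of the device and yet compares them between arms, so the phrase looks like shorthand for the start of treatment. It could matter only for PHQ-9, PCS and EQ-5D-5L, which are not collected at V3.
- **That 12% or 20% is the expected type I error.** Those figures come from an adverse corner. Milder inputs give 5% to 7%, and equal dropout with a growing true effect makes LOCF conservative.

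It is also fair to say that visits and payments are alike in both arms, that both receive adherence support, and that further sensitivity analyses may sit in an analysis plan not shown. Their absence is not the point here. What stands is that the article itself fixes the primary method. The un-imputed PPS analysis, and the promise to investigate FAS/PPS discrepancies, do not test it, because the PPS removes the premature withdrawals whose values LOCF fills in.

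**Conclusion.** The point holds in limited form and should be fixed. For participants with V3 but no V4, at most the assumed 20%, a week-4 score stands in for week 8 and is analysed as if observed. The week-8 effect is biased, in either direction, when share imputed times subsequent change differs between arms. The plausible size runs from nothing, through 0.5 to 1.1 points, to 2 points on the 100-point scale, and about 3 if higher-pain controls leave. All of these rest on assumed dropout splits, time course and correlations, and on reading the pilot scores as 0–10.

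A related ambiguity needs settling. If the FAS condition on primary efficacy data means the V4 score, the FAS holds week-8 completers only and LOCF never acts on the primary endpoint. The problem then becomes a completers-only primary analysis. The two sections have to be reconciled on either reading.

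**What to change.** - **Primary analysis.** Use a mixed model for repeated measures on usual pain at V3, V4 and V5 with arm, visit, arm-by-visit, baseline pain, baseline-by-visit and an unstructured covariance, taking the arm contrast at week 8. Alternatively, use ANCOVA after multiple imputation by arm with V3 and V5 in the imputation model.
- **LOCF.** Keep it at most as a sensitivity analysis.
- **FAS definition.** State which visit satisfies the condition on primary efficacy data, so that it agrees with the missing-data rule.
- **Wording.** State the no-baseline rule for both arms in terms of the start of allocated treatment.

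The cost is a change of protocol and analysis-plan wording, made before database lock, and modest programming. V3 and V5 are already scheduled, so no new data are needed. The sample size need not rise, because 216 already allows for losing 20%. The downside is reliance on a missing-at-random assumption, which should be stated.
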